## Abstract

**Background:**

Many studies have reported an association between epilepsy, nodding syndrome (NS), and onchocerciasis (river blindness). A high prevalence of epilepsy has been noted particularly in onchocerciasis hyperendemic areas where onchocerciasis is not or insufficiently controlled with mass ivermectin distribution. There is evidence that increasing the coverage of ivermectin reduces the incidence of epilepsy, and anecdotal evidence suggests a reduction in seizure frequency in onchocerciasis-associated epilepsy (OAE) patients who receive ivermectin. Finding an alternative treatment for epilepsy in these patients will have major consequences.

**Objective:**

The goal of the study is to assess whether ivermectin treatment decreases the frequency of seizures and leads to seizure freedom in OAE patients, including patients with NS. If we are able to demonstrate such an effect, this would strengthen the argument that onchocerciasis is causing epilepsy and therefore we should increase our efforts to eliminate onchocerciasis.

**Methods:**

We will conduct a randomized clinical trial in the Democratic Republic of Congo to compare seizure freedom in onchocerciasis-infested epilepsy patients who receive immediate ivermectin treatment with delayed (after 4 months) ivermectin treatment. All participants will simultaneously receive antiepilepsy drugs (AEDs) according to local guidelines for epilepsy treatment. The primary endpoint is seizure freedom defined as no seizures during the 4 month of follow-up. Secondary endpoint is significant (>50%) seizure reduction compared to baseline seizure frequency. Reduction of seizures will be compared between ivermectin and nonivermectin arms.

**Results:**

Start of enrollment is planned for August 2017, and we expect to have enrolled all 110 participants by December 2017. Results are expected in June 2018.

**Conclusions:**

If ivermectin treatment in addition to AEDs is able to lead to seizure freedom or significantly reduces seizure frequency in OAE patients, this will have major consequences for epilepsy treatment in onchocerciasis-endemic regions. Ivermectin is donated for free and in non Loa-Loa–endemic regions has negligible side effects. Reducing the burden of epilepsy will have a major impact on quality of life and socioeconomic status of families with affected members in Africa.

**Trial Registration:**

ClinicalTrials.gov NCT03052998; https://clinicaltrials.gov/ct2/show/NCT03052998 (Archived by WebCite at http://www.webcitation.org/6roFVQSG0)

## Introduction

### Onchocerciasis-Associated Epilepsy

Many studies have reported an association between epilepsy, nodding syndrome (NS), and onchocerciasis [1-4]. A meta-analysis of African population-based surveys showed a variation in epilepsy prevalence consistent with onchocerciasis prevalence, with epilepsy prevalence being increased, on average, by 0.4% for each 10% increase in onchocerciasis prevalence [2]. NS is an epileptic disorder occurring in children in onchocerciasis (river blindness) endemic regions, initially only observed in South Sudan, Uganda, and Tanzania [5]. NS occurs in previously healthy children, aged mainly from 5 to 18 years and is characterized by head-nodding, an atonic epileptic seizure [5,6]. Individuals may also develop other types of seizures and stunted growth. Many affected children not only suffer from recurrent seizures but also from severe cognitive, behavioral, and psychiatric problems [7,8]. NS should be considered part of a spectrum of onchocerciasis-associated epilepsy (OAE) disorders [9]. We recently suggested that these epileptic disorders share etiological factors related to *Onchocerca volvulus* infection and therefore considered ivermectin, used to treat onchocerciasis, as a treatment option for OAE [10].

### Ivermectin Treatment May Prevent Onchocerciasis-Associated Epilepsy

Ivermectin is effective against many types of parasites and is recommended every 6 months for treatment of onchocerciasis. Medication is taken orally and generally well tolerated [11]. Accumulating evidence is suggesting that ivermectin may prevent OAE. After the introduction of biannual mass treatment with ivermectin in 2012, no new NS cases have been observed in Northern Uganda [12]. In a recent age-matched case control study in Titule, Bas Uélé, in the Democratic Republic of Congo (DRC), 16/18 (89%) of patients with epilepsy had not taken ivermectin the year before they developed epilepsy, compared to 7/18 (39%) controls (*P*=.002) [13]. We recently visited several villages in the Mbam valley (an onchocerciasis-endemic area in Cameroon) where the prevalence of epilepsy in 1992 ranged between 4% and 8% and most epilepsy cases occurred in people aged younger than 20 years [3]. In 2015, after more than 15 years of administering ivermectin annually, nearly all epilepsy cases were in people over the age of 20 years, also suggesting a protective effect of ivermectin on the incidence of epilepsy ([name], personal communication). A similar age shift of epilepsy cases to older age groups after the introduction of ivermectin was reported in an onchocerciasis-endemic region in Nigeria [14]. With ivermectin distribution only once a year, it may take many years with high treatment coverage before a significant effect on the incidence of OAE is observed. Indeed, several months after the administration of one dose of ivermectin, microfilariae reappear and therefore create a risk for the infected individual to develop epilepsy. For this reason, in order to decrease the incidence of OAE more rapidly, at least biannual intake of ivermectin may be required.

### Pathophysiological Mechanism of Onchocerciasis-Associated Epilepsy

The pathophysiological mechanism of OAE remains unclear. In recent studies, *O volvulus* DNA was never isolated from cerebrospinal fluid (CSF) in patients with NS [15]. However, several of the patients enrolled in these studies had taken ivermectin in the past. In 1938, before the use of ivermectin, microfilariae in CSF were described by Casis Sacre [16] in Mexican patients with onchocerciasis with NS and Nakalanga-like clinical manifestations. Dead and live microfilariae were also found in 1959 by Mazotti [17] in CSF of patients with onchocerciasis treated with diethylcarbamazepine. In 1976, Duke et al [18] noted the presence of small numbers of *O volvulus* microfilariae in the CSF (<2 mf/mL) in 5 of 8 untreated heavily infected (>100 mf/mg skin) onchocerciasis patients. During diethylcarbamazine treatment, in 10 out of 11 heavily infected patients presenting with an ocular form of onchocerciasis, the numbers of *O volvulus* microfilariae in the CSF increased even up to 8 to 31 mf/mL [18]. Patients with *O volvulus* infection receiving diethylcarbamazine were reported to develop optic atrophy, probably because of a Mazotti reaction caused by dead microfilariae present in the optic nerve [19]. Perhaps this nerve could be an entry point of the microfilariae to the brain. Another explanation for the association between onchocerciasis and epilepsy could be the occurrence of an autoimmune response related to the *O volvulus* infection [20] leading to seizures.

Ivermectin acts on the chloride-dependent channels of both glutamate and γ-aminobutyric acid, interrupting neurotransmission in invertebrates. However, in humans, several mechanisms of brain protection exist, including P-glycoprotein, present on the apical face of endothelial cells of the blood-brain barrier and coded by the MDR1 gene [21]. Therefore in humans ivermectin generally does not enter the brain [21] and would not be able to kill microfilariae inside the brain. Ivermectin could, however, reduce the microfilariae load outside the brain and either reduce the risk that additional microfilariae penetrate the brain or reduce the neurotoxic immunological response caused by the microfilarae.

One dose of ivermectin eliminates microfilarae very rapidly [22]. A mathematical model predicted that microfilaridermia would be reduced by half 24 hours after the intake of ivermectin [23]. Therefore, if the microfilariae load plays an important role in causing OAE, it may be that ivermectin also has a rapid effect on the frequency of seizures.

### Ivermectin Treatment May Decrease Seizure Frequency in Patients With Onchocerciasis-Associated Epilepsy

In a study in Kabarole district in Uganda in 1992, 34/91 (37%) patients reported some decrease in either the frequency or severity of seizures after 1 dose of ivermectin (150 µg/kg) [24]. After being treated with ivermectin, 13/91 (14%) individuals had no seizures for 3.7 months (on average). Seizures were unchanged in 51/91 (56%), and worsened in 6/91 (7%) [24]. In a recent trial in the DRC comparing moxidectin (an anti- *O volvulus* experimental drug with a longer half-life than ivermectin) with ivermectin, 6 (80%) out of 7 *O volvulus*-infested patients with epilepsy became seizure free after treatment with moxidectin or ivermectin (the randomization code has not been broken yet). In one person, seizure frequency was significantly reduced over the 18-month follow-up period. In this person, microfilariae remained present in skin snips, although at a lower level than before the onchocerciasis treatment. In all subjects who became seizure free, the skin snips too became microfilaria free [[name], unpublished].

To assess whether ivermectin treatment may reduce the frequency of seizures and lead to seizure freedom, we intend to conduct a short proof-of-concept randomized clinical trial to compare immediate ivermectin treatment with delayed (after 4 months) ivermectin treatment in onchocerciasis-infested persons with epilepsy. The primary outcome is seizure freedom at 4 months. Reducing the burden of epilepsy will have a major impact on quality of life and socioeconomic status of families with affected members in Africa. If we are able to demonstrate an effect of ivermectin on the frequency of seizures, this would be an extra argument that onchocerciasis is causing epilepsy and that therefore we should increase our efforts to eliminate onchocerciasis.

## Methods

### Study Design

This is a proof-of-concept randomized treatment trial consisting of 2 treatment arms, immediate (arm A) and delayed (4 months later) ivermectin treatment (arm B). A computer-based, preplanned age and frequency of seizures stratified randomization list will be used. The trial will not be placebo-controlled as this will be costly and we do not expect this to greatly influence reporting of seizures, our primary outcome. Epilepsy patients in both arms will additionally receive antiepileptic drugs (AEDs) following local guidelines of epilepsy treatment in DRC. Study investigators collecting and analyzing data will be blinded for treatment.

### Study Population, Setting, and Enrollment

The trial will take place in selected villages in the Logo health zone, an onchocerciasis-endemic region in the Ituri province in the DRC, in areas where so far mass ivermectin administration has not been implemented but where the national onchocerciasis program is planning to start community-directed distribution of ivermectin in 2017. Pilot studies by our group in this area show prevalence estimates of OAE of approximately 5% [25].

Before starting, the village chief and community health workers will be informed of the purpose and specifics of our study. When permission is obtained, our medical team will visit the village and set up a mobile clinic. Patients who may fulfill eligibility criteria are selected and examined for a screening visit after informed consent is obtained from patient and/or caretaker in the local language (Alur). Patients who meet the enrollment criteria (see Textbox 1) are invited to participate in the treatment trial. Detailed information about the trial is given in local language, and enrollment informed consent is obtained.

Our study population consists of epilepsy patients aged 5 years and older with onchocerciasis and without other obvious risk factors for epilepsy.

### Trial Registration

The trial is registered at ClinicalTrials.gov [NCT03052998] and will be registered at the World Health Organization International Registry Network.

### Screening of Epilepsy Patients for Onchocerca volvulus Infection

After informed consent is obtained, trial candidates with epilepsy will be tested for the presence of antibodies to the parasite antigen OV16 with the SD BIOLINE Onchocerciasis IgG4 Rapid Test (Standard Diagnostics Inc). Also, a skin snip will be taken from the left and right iliac crests with a Holtz corneoscleral punch (2 mm). One sterilized punch will be used per subject. Each snip will be weighed on an analytical balance and incubated for 24 hours in isotonic saline in a well of a flat-bottomed microtiter plate. The microfilariae that emerge will be counted using an inverted microscope. The number of microfilariae in each well and the weight of the associated skin snip before incubation will be recorded. The mean of the skin microfilarial (mf) density (mf count/weight) of snip across all 4 skin snips will be calculated and recorded as mf/mg. Skin biopsies will then be stored in 90% ethanol to be tested for *O volvulus* by an in-house polymerase chain reaction method (supplemental methods).

### Diagnosis of Onchocerca volvulus Infection

Diagnosis of onchocerciasis infection will be made when microfilariae are detected in skin snip and/or antibodies to the parasite antigen OV16 are detected.

### Diagnosis of Epilepsy

To identify eligible epilepsy patients with generalized tonic clonic seizures, we will use a 10-item epilepsy questionnaire previously used in international epilepsy prevalence studies [26,27]. A person identified on the basis of this questionnaire as possibly a person with epilepsy will be examined by a neurologist to make an accurate diagnosis according to definitions proposed by the International League Against Epilepsy [28]. A case of epilepsy will be defined as a patient who has had (1) at least 2 times, unprovoked and without fever, lost consciousness with convulsions with a minimal time difference of 24 hours between the 2 events or (2) 1 unprovoked seizure and a probability of future seizures similar to the general recurrence risk after 2 unprovoked seizures. Detailed questions including the age at seizure onset, seizure frequency, and family history of seizures are part of the baseline questionnaire. The eligibility criteria are listed in Textbox 1.

Selection criteria.Inclusion criteria:Age 5 years and olderSigned informed consent formNormal neurological development until onset of epilepsyOnset of epilepsy between ages of 5 and 18 yearsSeizure frequency of ≥2 seizures per monthPresence of microfilariae in skin snip and/or antibodies against OV16Generalized (primarily or secondarily) tonic clonic seizures are presentExclusion criteria:Ivermectin intake in the last 9 monthsPregnancy or breastfeedingKnown or suspected allergy to ivermectin*Loa Loa* microfilariae in blood^a^Epilepsy with known cause (eg, severe head trauma, perinatal asphyxia, patients with a history of cerebral malaria, meningitis, or encephalitis)Concomitant acute illness or chronic medication useChronic alcohol or substance useUse of antiepilepsy drugs in the past 2 weeks

^a^Treatment with ivermectin in persons with *Loa Loa* co-infection may cause fatal encephalopathy.

Blood samples will be tested for *Taenia solium* antibodies and antigen, but in the absence of a point-of-care test, results will only become available after screening. Therefore these test results are not part of the eligibility criteria. However, they will be taken into account in analyzing the results.

### Ivermectin Treatment Strategy

Following recommendations, 1 dose of 150 µg/kg ivermectin (Mectizan) will be administered orally, and treatment will be directly observed. Ivermectin is generally well tolerated. Common side effects of ivermectin include fever, itching, skin rash, edema, myalgia, and headache.

### Anti-Epileptic Drug Treatment Strategy

We designed a standard epilepsy treatment protocol for both treatment arms. To summarize, we will start with phenobarbital 100 mg once a day which may be increased to 150 to 200 mg per day after 2 months if there is insufficient seizure reduction (less than 50% reduction of seizure frequency). If there are contraindications for use of phenobarbital (intellectual or behavioral disorders) or persistent side effects, carbamazepine will be prescribed (in adults initial dose 100 to 200 mg per day, maintenance dose 400 to 1400 mg; in children initial dose is 5 mg/kg per day, maintenance dose 10 to 30 mg/kg per day). In the case of side effects related to carbamazepine, we will start with sodium valproate (in adults initial dose 400 mg per day, maintenance dose 400 to 2000 mg per day; in children initial dose 15 to 20 mg/kg per day and maintenance dose 15 to 30 mg/kg per day). In the case of carbamazepine and sodium valproate, we will prescribe initial dose in all patients and will increase this to the lowest maintenance dose at 2-week visit. In case of dose-determined side effects, dose reduction is permitted. Dose may be increased at the 2-month visit if there is insufficient seizure control (less than 50% reduction in seizure frequency). Individual treatment decisions will be made by the team physician who has received specific training in epilepsy treatment and can consult with the team neurologist. Patient and family will be informed of the following regarding epilepsy treatment [29]:

Delay in onset of effect and the time course of treatmentPotential side effects and the risk of these symptoms (seek help promptly if these are distressing)Risk of abrupt discontinuation/withdrawal symptoms on missing dosesNeed for regular follow-up

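### First-line phenobarbital is printed as one flat dose from age 5, with no child dose, mg/kg cap or weight floor, although both fallback drugs are dosed in mg/kg for children

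*Protocol article*

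**What the plan says.** The Anti-Epileptic Drug Treatment Strategy section describes one regimen for both arms and presents the text as a summary of a standard treatment protocol. For the first-line drug, "we will start with phenobarbital 100 mg once a day which may be increased to 150 to 200 mg per day after 2 months". The increase is optional and applies only when seizure frequency has fallen by less than 50%. No separate phenobarbital dose is given for children.

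For the two fallback drugs, the same paragraph separates adults from children:
- Carbamazepine: "in children initial dose is 5 mg/kg per day, maintenance dose 10 to 30 mg/kg per day".
- Sodium valproate: "in children initial dose 15 to 20 mg/kg per day and maintenance dose 15 to 30 mg/kg per day".

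Ivermectin is also dosed by weight, at 150 µg/kg (Ivermectin Treatment Strategy). Patients are eligible from age 5, and the selection criteria set no minimum weight.

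Several provisions bear on tolerability. Where phenobarbital is contraindicated because of intellectual or behavioral problems, "or persistent side effects, carbamazepine will be prescribed". The section adds: "In case of dose-determined side effects, dose reduction is permitted". It also says: "Individual treatment decisions will be made by the team physician", who is trained in epilepsy treatment and can consult the neurologist. Study Design says that AEDs are given "following local guidelines of epilepsy treatment in DRC".

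**The concern.** Followed as printed, a small 5-year-old and an adult have the same phenobarbital start and the same permitted ceiling. Phenobarbital is the drug that everyone without a contraindication starts on, and it is the only one of the three AEDs without a child dose. Because the paragraph does give child doses for the other two, a reader at the site could reasonably take 100 mg as the dose for all ages.

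What is at stake is tolerability and safety in the smallest participants. The article itself treats AED side effects as a threat to adherence: Compliance schedules the week-2 visit to limit withdrawal from AEDs, and the Discussion names side effects as a cause of noncompliance. AED treatment is also meant to continue after the trial, so a poorly fitted dose could persist.

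**Working it through.** The article prints no mg/kg figure for phenobarbital, so there is no figure of the plan's own to reproduce. The check is division of the printed dose by body weight.

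**Inputs from the article:** phenobarbital 100 mg/day at the start; 150 to 200 mg/day as the optional step after 2 months; entry from age 5.

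**Assumed inputs (the article gives no weights):** 15 to 20 kg for a small child, 55 kg for an adult.

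**Formula:** dose in mg/kg per day = daily dose in mg / body weight in kg.

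| Daily dose | 15 kg | 20 kg | 55 kg |
|---|---|---|---|
| 100 mg (start) | 100/15 = 6.7 | 100/20 = 5.0 | 100/55 = 1.8 |
| 150 mg (step, lower) | 150/15 = 10.0 | 150/20 = 7.5 | 150/55 = 2.7 |
| 200 mg (ceiling) | 200/15 = 13.3 | 200/20 = 10.0 | 200/55 = 3.6 |

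Because the dose is flat, the child-to-adult ratio is the same at every step: 55/20 = 2.75 to 55/15 = 3.7.

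**Start against ceiling.** The child's starting dose (5.0 to 6.7 mg/kg) already exceeds the adult's ceiling (3.6 mg/kg). The weight at which 100 mg equals the adult ceiling per kg solves 100/w = 200/55, so w = 27.5 kg. Below that weight, the start alone exceeds what a 55 kg adult receives at 200 mg. The step to 200 mg doubles the child's mg/kg dose. Both points of the regimen therefore need a child rule.

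**Timing of the safeguards.**
- Dose reduction and the switch for persistent side effects come after the child has been dosed.
- The side-effect visit at week 2 and the visit at month 1 fall before the optional step. The next scheduled visit after that step is month 3.
- AED blood levels are measured to assess compliance, and Table 1 shows the only post-baseline blood exam at month 4. They are not described as a guide to the month-2 dose.
- Physician discretion, the local guidelines and the contraindication can act before dosing. The first two supply no printed phenobarbital limit for children.

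**The case against.** The strongest defense is condensation. The paragraph is a declared summary, the full treatment protocol is not shown, and the local guidelines are cited but not reproduced. A child dose may well stand in one of them, and detail of that kind is commonly left out of an article. This stands in part: the trial's actual dosing may be sound. It does not fully excuse the text, because the summary does not leave pediatric dosing to another document. It prints child doses for two of three drugs and an undivided dose for the third.

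The second defense is the list of safeguards. A trained physician decides individually with neurologist support. The increase is optional and comes only after 2 months at 100 mg. A structured questionnaire asks about known phenobarbital side effects, and a Data Safety Monitoring Board reviews safety. Patients with intellectual or behavioral problems go to carbamazepine, which has a child dose. The Introduction reports severe cognitive and behavioral problems in many children with nodding syndrome, so some of the children at issue may never receive phenobarbital. All of this stands and lowers the severity.

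Three stronger readings are tempting, and the article supports none of them:
- **Children would be overdosed.** The article gives no mg/kg limit for phenobarbital, so the figures above show a contrast with adults, not a breach.
- **Only the ceiling matters.** A reader might infer this because the carbamazepine and valproate child rules reach the adult top dose only at 1400/30 = 46.7 kg and 2000/30 = 66.7 kg. Those weights describe other drugs and say nothing about phenobarbital tolerability. The phenobarbital start already exceeds the adult ceiling per kg in a 15 to 20 kg child.
- **The treatment comparison is biased.** Both arms follow the same regimen and randomization is stratified by age, so the missing child dose does not itself favor either arm.

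**Conclusion.** The point holds as a low-severity matter of tolerability and safety. The printed first-line dose has no provision for body weight in a trial that admits patients from age 5. At the assumed weights, a small child receives about 2.75 to 3.7 times the adult mg/kg dose at the start and at the ceiling alike.

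The size rests on the assumed 15 to 20 kg and 55 kg. The article gives no age or weight distribution, so the number of children affected is unknown and may be small. Sample size, type I error and the comparison between arms are unaffected. Whether the gap lies in the trial's dosing rules or only in the article's summary cannot be settled without the full treatment protocol.

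**What to change.** For children, state a mg/kg phenobarbital start and a mg/kg cap on the month-2 step, or a body weight below which the flat doses do not apply. The trial neurologists should set the figures in line with the local guidelines, and they should apply identically in both arms. If the full treatment protocol already holds a child dose, correct the Anti-Epileptic Drug Treatment Strategy section to state it.

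The cost is one protocol sentence and a dosing card for the sites. Weight is already measured at baseline and follow-up (Baseline and Follow-Up Procedures), so no new data are needed. The downside is that tablets may need splitting for small children.

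### Nothing secures that the initial antiepileptic drug is chosen before allocation is known, and the reason for a later change, which can decide nonresponse, can come from an unblinded prescriber

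*Protocol article*

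**What the plan says.** Under Anti-Epileptic Drug Treatment Strategy the article describes a common scheme: "We designed a standard epilepsy treatment protocol for both treatment arms". The first step is fixed: "we will start with phenobarbital 100 mg once a day which may be increased to 150 to 200 mg per day after 2 months" if the seizure response is insufficient. The exit from phenobarbital is a judgement: "If there are contraindications for use of phenobarbital (intellectual or behavioral disorders) or persistent side effects, carbamazepine will be prescribed". No threshold is given. For carbamazepine the starting dose is a range ("in adults initial dose 100 to 200 mg per day, maintenance dose 400 to 1400 mg"), raised to the lowest maintenance dose at the 2-week visit. Further increases at 2 months are optional, and side effects allow dose reduction or a switch. Within this scheme, "Individual treatment decisions will be made by the team physician who has received specific training in epilepsy treatment", with the team neurologist available for advice.

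Under Study Design there is no placebo, and blinding is described in one sentence: "Study investigators collecting and analyzing data will be blinded for treatment". Under Ivermectin Treatment Strategy the single dose is directly observed. Table 1 puts eligibility, the patient questionnaire and the neurological assessment at t=-1, and puts AED and ivermectin together in one administration row whose first mark is at t=0. AED use in the 2 weeks before entry is an exclusion criterion.

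Randomization is stratified by age and seizure frequency, and the primary test controls for baseline seizure frequency. Under Sample Size Calculation, a patient whose AED regimen is adapted because seizures increase counts as a nonresponder, while changes for side effects or drug interactions do not count as failure.

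**The concern.** The trial attributes a difference in seizure freedom to ivermectin on the footing that background AED treatment is the same in both arms. The article itself expects 50% seizure freedom on AEDs alone, so AED treatment is a strong driver of the primary endpoint. If the prescriber knows who receives ivermectin now, two routes to bias are open.

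- **Initial choice.** A judgement about the contraindication, or about the starting dose of the alternative, could differ by arm. Intention-to-treat analysis does not remove the effect of arm-dependent co-treatment. Adjusting afterwards for a drug chosen with knowledge of allocation means adjusting for a post-randomization variable.
- **Later changes.** The reason attached to an AED change separates nonresponse from no penalty in the primary endpoint. If the prescriber supplies that reason, an unblinded judgement enters the outcome directly.

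**Working it through.** **Who can know the arm, and when**

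1. Ivermectin is visible: no placebo (Study Design), directly observed (Ivermectin Treatment Strategy).
2. The blinding sentence names those who collect and analyze data. The team physician as prescriber is not named.
3. Every participant's trial AED is started in the trial, because recent AED use is excluded (selection criteria).
4. Table 1 first marks AED and ivermectin at t=0. The history and neurological assessment that inform the contraindication are at t=-1.
5. No sentence says that the AED is chosen before allocation is known, and none says that it is chosen after.

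The information for an early choice is therefore already collected, but the order of steps is not secured.

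**Where the reason for a change enters the endpoint**

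An AED change for increasing seizures makes a nonresponder; one for side effects or interactions does not. The optional 2-month increase is triggered by less than 50% seizure reduction, which is named in neither class, so someone must place it. The article does not say who.

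**The plan's own figure**

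Inputs from Sample Size Calculation: 50% versus 80%, 90% power, 5% level, 1:1. With the pooled-variance formula,

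n per arm = [z_α·√(2·0.65·0.35) + 1.2816·√(0.25 + 0.16)]² / 0.30².

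With z_α = 1.960 (two-sided) this is 51.01, rounded up to 52 per arm, 104 in total; 104/0.95 gives 110. The plan's figure is reproduced. With z_α = 1.645 (one-sided, as the test is specified) it is 41.4, so 42 per arm, 84 in total. That mismatch in sidedness is a separate matter. The fix below does not change the sample size.

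**Illustration of what an AED imbalance would do**

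Assumptions, none from the documents: ivermectin has no effect, and AED differences alone produce a gap d (immediate minus delayed) in seizure freedom, centred on 50%. For example, a 20-point difference in effect between AED regimens times a 5, 10, 20 or 30 point imbalance in their use gives d = 1, 2, 4 or 6 points. With 52 per arm and the one-sided 5% test,

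P(reject) = Φ[(d − 1.645·SE₀)/SE₁], with SE₀ = √(2·0.5·0.5/52) = 0.0981 and SE₁ = √{[p_A(1−p_A) + p_B(1−p_B)]/52}.

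For d = 0.04: SE₁ = 0.0980, so (0.04 − 0.1613)/0.0980 = −1.238 and Φ = 10.8%.

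| Assumed d | Favouring immediate arm | Reversed |
|---|---|---|
| 1 point | 6.1% | 4.0% |
| 2 points | 7.5% | 3.2% |
| 4 points | 10.8% | 2.0% |
| 6 points | 15.0% | 1.2% |

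A second assumed case gives the same order. Take 55 per arm, 50% seizure freedom on the first AED and 35% on the alternative, with 10% of the immediate arm and 30% of the delayed arm on the alternative. Then p_A = 0.9·0.50 + 0.1·0.35 = 0.485 and p_B = 0.7·0.50 + 0.3·0.35 = 0.455, so d = 0.03. Rejection is 9.2%, or 2.5% when reversed.

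The loss in the other direction: if ivermectin works as planned (80%) but better background treatment lifts the delayed arm from 50% to 55% or 60%, one-sided power with 52 per arm falls from 95.0% to 86.8% or 72.4%.

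**The case against.** The strongest objection is that the AED scheme is a standard one. The first drug, its starting dose and the order of alternatives are the same in both arms, with stated triggers and visits, and a neurologist can be consulted. A reader might infer that drug and dose are simply left to the physician; the text does not support that. Initial discretion is limited to the contraindication judgement and the alternative's starting dose. This stands and narrows the point.

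A reader might also infer from Table 1 that the AED is chosen after allocation. The row shows administration, not choice. It also merges a single-dose drug with a daily one and is marked at every visit from t=0, while the AED pill count is already marked at t=-1. The table is too coarse to fix the order of steps, so a choice at screening is equally compatible with it. Nor does it follow that AED cannot be a baseline variable: contraindication status assessed at t=-1 could serve.

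The article's remark on "severe cognitive, behavioral, and psychiatric problems" concerns children with nodding syndrome. They are only part of the trial population, and no share is given, so it cannot be said that the contraindication will arise in many participants. Nor do the documents say whether the team physician is also one of the blinded data collectors.

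Finally, the AED section is introduced as a summary, and a fuller protocol may set the order of steps. That would excuse a missing detail. It does not dispose of the point: the article positively states open dosing, limited blinding, prescriber discretion and an outcome rule that depends on the reason for an AED change. Together these leave a gap that a small procedural step closes.

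**Conclusion.** The concern holds in limited form. Under a common AED scheme, the prescriber keeps some discretion at the start and more later, is not stated to be blinded, and works in an open trial in which AED and ivermectin begin at the same step. The initial AED is therefore not secured as a baseline variable, and the reason for later changes can enter the primary endpoint through someone who knows the arm.

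The documents do not show that an imbalance will occur, in which direction, or how large it would be. The error range of about 6% to 15% rests on assumed AED-driven gaps of 1 to 6 points favouring immediate ivermectin and no ivermectin effect; a reversed gap makes the test conservative and can hide a true effect. The change is worth making because it costs little, not because a bias of a given size has been shown. Nothing here bears on which drug or dose is right.

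**What to change.** 1. **Lock the initial choice.** On the t=-1 form the physician records contraindication status, the intended initial AED and its starting dose. Allocation is opened only after that entry is locked. Tabulate AED by arm, and use the locked entry as a baseline variable in a sensitivity analysis.
2. **Blind the classification of changes.** Record every later AED change with its date, dose and seizure-diary counts. The investigators already stated to be blinded, not the prescriber, classify the reason for the nonresponder rule.
3. **Report what remains.** Step 1 protects only the initial choice. Report later increases, reductions and switches by arm.

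The cost is a few form fields at a visit where the assessments already take place, one line on the order of steps, and a little classification work. The AED decision must be finished before allocation is opened. There is no added visit, and the sample size of 104, or 110 enrolled, is unchanged.
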